### 2.4. Study Population

The study population for the quantitative study involves pregnant mothers registered by VHTs on suspecting the pregnancy. The study will follow these participants from pregnancy until six weeks post-delivery. For qualitative data (key informant interviews and focus group discussions), mothers shall be enrolled towards the end of the study period. Enrolment for the qualitative process evaluation will also cover VHTs, health facility staff, district health leaders and staff from the World Vision Uganda office in the department of health. To be included, women have to have either an ANC card with a child health card or a mother-child passport. Participants shall be considered discontinued if they migrate from the location included into the study at any point in time during the community health worker (CHW) follow up period.

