### 2.5. Conceptual Framework

The proposed study aims to determine the effect of ttC on pregnancy outcomes and newborn survival in rural Uganda. Specifically, the study aims to ascertain the extent to which ttC improves uptake of timely goal-oriented ANC with a focus on the recommended visits, and to determine whether ttC contributes to the recommended hygienic birth practices. Additional aims are to establish the extent to which ttC improves essential newborn care practices during the newborn period, and to ascertain the extent to which ttC fosters positive male involvement in pregnancy and newborn care. Finally, the study aims to ascertain the relationship between ttC implementation and appropriate pregnancy weight gain by end of pregnancy and appropriate birth weight.

We expect that if the VHTs implement ttC effectively, there will be an increased uptake of ANC services in the intervention districts, including the timely attendance of goal-oriented ANC services, and the development and implementation of a birth plan. In addition, we expect essential newborn care improvements at the levels of the health facility and the community, aimed at newborn survival within the first 28 days of life, as well as improved visible male involvement in MNH care, including escorting the pregnant women for at least one ANC where couple human immunodeficiency virus (HIV) counselling and testing occurs. Ultimately, we expect these improvements to result in appropriate pregnancy outcomes and newborn survival (see Figure 1).

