### 2.9. Study Timelines

The study will fit into approximately two years from the time of the first participants allocation of intervention. The allocation of study timelines has been allocated in three different thematic areas of enrolment, intervention and assessments pre-and post-exposure ttC. The study period will focus on enrolment, allocation of treatment and post allocation. This will be concluded by the close out processes. The allocation of timelines in the study was assisted by the standard protocol items: recommendation for international trails (SPIRIT) timetable shown in the Table 3 below.

Women shall be enrolled in the study as they get pregnant and attend their first ANC to be able to acquire their Mothers passports and get referral to CHWs. Enrolment shall follow the stated criteria through an eligibility assessment. CHWs shall identify as many pregnant women as possible in order for the study eligibility screening to be done so that to attain the required sample. For this study, 1218 participants have to complete the interventions and therefore any drop outs before the 6 weeks after child birth will be replaced by another woman. The anticipated eligibility screening, follow up loss and eventual hitting the targeted number of participants is presented in the Consolidated Standards of Reporting Trials (CONSORT) flowchart in Figure 2 below:

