### 2.10. Sampling Procedure

A multi-stage sampling technique will be employed to select study participants. A total of 20 clusters of sub-counties will be selected and included in the study, based on the power calculation. Sub-counties with largest numbers of pregnant mothers registered by the VHTs will be included to ensure that the estimated study sample size is met. This will be used to increase the level of efficiency of sampling and each cluster will be considered as a sampling unit. At the beginning of the study, the team will consult the ttC registers from the VHTs in Hoima and the VHT registers from Masindi to assess the pregnancy registration per sub-county. For each sub-county, six villages will be randomly selected, with each village providing 10 households.

At the household, selection of pregnant mothers to be included in the study will be done systematically. In this probability sampling, participants will be selected from a larger population of pregnant mothers according to a random starting point and a fixed periodic interval. This periodic interval will be determined beforehand as two, which means that assuming the starting point is one as the first serial number on the VHT register, every pregnant mother with an even serial number will be selected to participate in the study, that is, 2, 4, 6, 8, etc. The sampling procedure is presented in Figure 3.

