**Figure 3 mps-03-00073-f003:**
[figure not shown]
The sampling flow framework.

**Table 1 mps-03-00073-t001:** Timed and targeted counselling (ttC) visits by village health teams (VHTs) to mothers during pregnancy or after childbirth.

Visit	Timing	Services Delivered by the VHTs
1	Before or at 3 months	Focuses on suspected pregnant mothers registered as ttC candidates. They are counselled on how to care for themselves during pregnancy, a list of danger signs during pregnancy is explained, and the family is encouraged to notify the VHT in the case of any of these danger signs. Families are counselled on what to do during pregnancy and when giving birth. Women pregnant for less than three months are advised to start antenatal care at three months.
2	At 4 months of pregnancy	This is to affirm that the pregnant mother went for ANC. The pregnant women are encouraged to go for the second ANC visit. Pregnant women are educated on the advantages of exclusive breastfeeding of children until 6 months of age and continuous breastfeeding until they reach the age of 2. Advantages of giving birth in a health facility and hand washing will be highlighted during this visit.
3	At 6 months of pregnancy	Discuss the birth plan, timing and place of the birth, exploring potential challenges faced by expectant mothers in reaching the health facility and ways of overcoming these challenges. Expectant mothers are given information on the different family planning methods and where to go for services, and are encouraged to utilize one of the methods after delivery.
4	8 months of pregnancy	The mother is educated about the early signs of true labor, danger signs during labor will be explained to the households, as well as appropriate action to take in the case of these danger signs. The mother is also encouraged to deliver at a health facility and have some emergency money available. This is also the visit at which the mother needs to have a clean birthing kit available (the “Mama Kit” [23]).
5–7	The newborn period	This visit is done three times in the first week after birth, on Days 1, 3 and 7. The VHT ensures that exclusive breastfeeding and essential maternal and newborn care are not only understood but also practiced. Mothers are educated on the need to seek health care if the neonate develops fever and/or a cough, and the need to go for routine growth monitoring and immunization.

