No	Variable	Description of Variable	Tool to Be Used
Dependent Variables			
1	Appropriate pregnancy weight gain at end of months pregnancy	Pregnancy weight gain of 11.5 kg to 16 kg by the end of the pregnancy	SQ
2	Newborn morbidity within the first 28 days of life	Newborn morbidity (focusing on cord infections, sepsis, asphyxia, fever, common flu and cold and diarrhea, pneumonia) within the first 28 days of life	SQ and ttCR
3	Appropriate birth weight	Appropriate birth weight of 2.5 kg or more	SQ
4	Mortality of newborns and mothers	If the mother died during pregnancy or childbirth, if the baby died either during pregnancy, childbirth or within the first 28 days of life.	SQ and ttCR
5	Overall maternal wellness	During pregnancy or newborn period, a mother does not develop sepsis, urinary tract infections, obstruction during birth or any danger signs during this period.	SQ and ttCR
Independent Variables			
1	Uptake of timely goal-oriented ANC	With a focus on the recommended four visits, the associated recommended services offered during these visits and timeliness of attendance.	VHTR, SQ and ttCR
2	Clean birthing practices	Birth attended by a skilled health provider, delivery happened in a health facility and a mama kit was used during the process.	SQ and ttCR
3	Essential newborn care practices (ENC) during the newborn period	Early initiation of breastfeeding, cord care practices, baby thermal care, sustained breastfeeding and baby WASH practices.	SQ and ttCR
4	Positive male involvement in pregnancy and newborn care	Man participates in at least one ANC, does an HIV test with the mother, available during birth, supports mother to help her rest, contributes finances for related logistics.	SQ

Notes: SQ: Study questionnaire, ttCR: ttC register, VHTR: Ugandan VHT household register.

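### Entry requires an ANC card or passport obtained at first ANC attendance, so the cohort is conditioned on a behaviour that ttC is meant to change

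*Protocol article*

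**What the plan says.** Section 2.4 gives two descriptions of who is studied. The population is "pregnant mothers registered by VHTs on suspecting the pregnancy", but the eligibility sentence reads "To be included, women have to have either an ANC card with a child health card or a mother-child passport". Section 2.9 gives a time of entry that fits the second description and not the first: "Women shall be enrolled in the study as they get pregnant and attend their first ANC to be able to acquire their Mothers passports".

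ANC attendance is also what the intervention targets. Section 2.5 names uptake of timely goal-oriented ANC as the first specific aim and expects that "there will be an increased uptake of ANC services in the intervention districts, including the timely attendance of goal-oriented ANC services". Table 4 describes the ANC variable as "With a focus on the recommended four visits, the associated recommended services offered during these visits and timeliness of attendance". Table 1 schedules ttC visit 1 at or before three months, for women whose pregnancy is only suspected, and states: "Women pregnant for less than three months are advised to start antenatal care at three months".

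On registers, Section 2.10 says that, to assess pregnancy registration per sub-county, "the team will consult the ttC registers from the VHTs in Hoima and the VHT registers from Masindi". Section 2.11 makes the VHT household register the basis of entry at both sites, but also calls the ttC register an entry point. Section 3.2 plans to hand out cards to all pregnant women at first contact, as a remedy for recall bias.

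**The concern.** Registration on suspicion and enrolment at first ANC are different time points and yield different populations. If the second rule is applied, a woman who never attends ANC cannot enter in either district. She is the woman in whom a programme that promotes ANC has most to change.

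The rule also need not act equally in the two districts. In Hoima, ttC visit 1 can reach a woman before she qualifies and can affect whether and when she qualifies. Entry is then a consequence of treatment, and comparing only those who entered is a comparison conditioned on a post-treatment event. If ttC brings reluctant attenders into the Hoima cohort while their counterparts in Masindi stay out, the two cohorts differ for a reason that has nothing to do with the effect of ttC on any given woman. At stake is the interpretation of the ANC comparison, the study's first specific aim.

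**Working it through.** **Order of events.** Under Table 1, a ttC woman is counselled at or before three months and told to start ANC. Under Section 2.9 she is enrolled when she attends. Counselling therefore comes before enrolment and is aimed at the event that triggers it. Section 1 reports that nationally 29% of women make a first visit in the first trimester. The other 100 - 29 = 71% attend later or never, so under usual care most women could not enter until after the visit 1 window, if at all.

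**Inputs for an illustration.**
- Control rate of four or more ANC visits among all pregnant women: 60% (the national figure in Section 1).
- True ttC rate: 70%. This is an assumption, taken as 60% plus the 10-point planning effect in Section 2.8.
- Share of pregnant women meeting the entry rule, *a*C (control) and *a*T (ttC): assumptions, because the documents give none.
- Group size: Section 2.8 states 609. It follows from the stated 1107: 1107 × 1.10 = 1217.7, rounded to 1218, and 1218 / 2 = 609. It is used here only for power.

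**Formula.** If every woman with four or more visits meets the entry rule, the rate among enrolled women is the rate among all pregnant women divided by the entry share. The observed difference is 0.70/*a*T - 0.60/*a*C.

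| *a*C / *a*T | Control cohort | ttC cohort | Observed difference | Power, 609 per arm, clustering ignored |
|---|---|---|---|---|
| 100% / 100% | 60.0% | 70.0% | +10.0 | 0.96 |
| 90% / 90% | 0.60/0.90 = 66.7% | 0.70/0.90 = 77.8% | +11.1 | 0.99 |
| 90% / 95% | 66.7% | 0.70/0.95 = 73.7% | +7.0 | 0.76 |
| 80% / 90% | 0.60/0.80 = 75.0% | 0.70/0.90 = 77.8% | +2.8 | 0.21 |
| 80% / 100% | 75.0% | 0.70/1.00 = 70.0% | -5.0 | wrong sign |

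**Where the direction turns.** With *a*C = 90%, the observed difference equals 10 points when *a*T = 0.70/(0.10 + 0.60/0.90) = 0.70/0.767 = 91.3%. Below that the effect is overstated; above it, understated. The sign reverses when *a*T exceeds *a*C × 0.70/0.60. That is 93.3% when *a*C = 80%, and it cannot happen when *a*C = 90%, since 0.90 × 7/6 = 105%. A reversal therefore needs a large difference in entry, while a visible distortion needs only a small one.

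**The case against.** **Cards at first contact.** The strongest answer is the plan in Section 3.2. If first contact means the VHT's own contact, before any ANC visit, the card rule would exclude few women or none. The documents leave the term open. Section 2.9, however, ties the passport and enrolment to the first ANC visit, and Section 3.2 offers the cards against recall bias, not as a change to eligibility. The same section notes that late ANC delays inclusion, but only as a recruitment difficulty. The plan could solve the problem, but it does not do so as written.

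**Different registers.** A reader might infer from Section 2.10 that the two cohorts are drawn from different registers. The documents do not support that. The sentence concerns counting registrations per sub-county; women are then picked by serial number on the VHT register, and Section 2.11 requires the VHT household register at both sites. What stands is narrower: Section 2.11 also makes the ttC register an entry point, and the abstract describes that register as an additional tool for the study area.

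**A known direction of bias.** A reader might infer that the ANC effect must shrink. It need not: equal entry shares of 90% inflate it to +11.1.

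**Earlier entry and more counted losses in Hoima.** Table 4 counts a death "if the baby died either during pregnancy, childbirth or within the first 28 days of life" and states no starting gestation, so earlier entry in one district would expose more fetal losses to being counted there. But no gestational age at entry is given for either district, and Table 2 has control VHTs promoting early ANC as well. Earlier entry in Hoima is possible, not documented. This part can also be handled by outcome definition and analysis, which an article may leave to a fuller document.

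**Selection of mothers with a surviving child.** A reader might infer this from the child health card. Nothing says that the card depends on the child's survival, and the passport is an alternative route.

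**Conclusion.** The point holds for the entry rule. Sections 2.4 and 2.9 conflict on when a woman becomes eligible. If the card and first-ANC rule is followed, never-attenders are excluded and the two cohorts can differ through the intervention itself. Adjustment for measured covariates cannot bring back women who were never enrolled.

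The size and direction are unknown. A true +10 points reads as anything from +11.1 to -5.0 across the four pairs of entry shares. That range rests on the assumed 70% ttC rate, the assumed shares, and the premise that every woman with four or more visits meets the rule. It shows sensitivity and is not an estimate. The conflict should be resolved before the ANC comparison is relied on. The concern about fetal loss is secondary and conditional on a difference in entry gestation that the documents do not establish.

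**What to change.** 1. Remove possession of a card or passport as an entry condition. Keep these records as a data source only.
2. Enrol sampled women at VHT registration, from the VHT household register in both districts, whether or not they have attended ANC.
3. Reconcile Sections 2.4, 2.9, 2.10, 2.11 and 3.2 so that they name one time and one register of entry. Remove the ttC register as a separate entry point in Hoima (it can remain the process-evaluation tool), and say what first contact means.
4. Flag mothers already enrolled under the card rule and report the ANC comparison with and without them.
5. Because gestational age at entry may differ by district, report newborn death per live birth separately from fetal loss. Count fetal loss from a common gestational age, among women enrolled before it.

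**Cost.** On paper this is a change to the eligibility text and the Table 4 wording. In the field it is more than that: Table 3 shows screening and consent from February 2019, so a change during enrolment would mix two entry rules, which is the reason for step 4. Some women without cards will contribute recalled rather than recorded data, and the share of recalled data should be reported by district.

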### 2.5. Conceptual Framework

The proposed study aims to determine the effect of ttC on pregnancy outcomes and newborn survival in rural Uganda. Specifically, the study aims to ascertain the extent to which ttC improves uptake of timely goal-oriented ANC with a focus on the recommended visits, and to determine whether ttC contributes to the recommended hygienic birth practices. Additional aims are to establish the extent to which ttC improves essential newborn care practices during the newborn period, and to ascertain the extent to which ttC fosters positive male involvement in pregnancy and newborn care. Finally, the study aims to ascertain the relationship between ttC implementation and appropriate pregnancy weight gain by end of pregnancy and appropriate birth weight.

We expect that if the VHTs implement ttC effectively, there will be an increased uptake of ANC services in the intervention districts, including the timely attendance of goal-oriented ANC services, and the development and implementation of a birth plan. In addition, we expect essential newborn care improvements at the levels of the health facility and the community, aimed at newborn survival within the first 28 days of life, as well as improved visible male involvement in MNH care, including escorting the pregnant women for at least one ANC where couple human immunodeficiency virus (HIV) counselling and testing occurs. Ultimately, we expect these improvements to result in appropriate pregnancy outcomes and newborn survival (see Figure 1).

### 2.6. Intervention

The ttC intervention will be rolled out as a behavioral change communication model for the first 1000 days. For ttC to be implemented, a five-day central hands-on training is conducted for the VHTs (intermediaries), using a two-way counselling approach (participatory approach). The training will be conducted by VHT supervisors who are trained as trainers in the course for 10 days. These VHTs are then expected to translate the acquired knowledge to the expectant mothers and mothers with neonates as they deliver the ttC package during their home visits.

In the WHO’s review of global CHW training resources [18], ttC emerged as one of the most comprehensive curricula available in terms of its range of technical content, and spectrum across the continuum of care. ttC takes a life-cycle approach, focusing on supporting for the period from pregnancy up to two years of age. We believe that providing care on this continuum offers the best opportunity to ensure that children are on a path to life-long health. Taking a more family-centered approach, in ttC VHTs learn practical skills for addressing barriers to MNH, promoting involvement of fathers, and enabling CHWs to identify barriers to health [19].

VHTs are taught how to handle the household heads, any other influential individuals and the expectant mothers or mothers with neonates. During the training, the VHTs are equipped with a participant’s manual, a ttC-specific household register to note down all pregnant mothers and kick-start the timely follow-up process as scheduled in the ttC guideline [20].

The ttC visits are at given times in the first 1000 days window to pass on a given message, to trigger the household to support the mother to go for a given service at the health centre. The visits that the VHT makes are in line with the Ministry of Health (MoH) goal-oriented ANC [21] services package, the institutional delivery framework of the road to the reduction of maternal and newborn death in Uganda [22] including the essential newborn care at the facility and the community level. For this study, our focus is on the value of the four visits made during pregnancy, the three visits made when the child is in the newborn period for essential newborn care practices and a fourth visit at six weeks to enhance exclusive breastfeeding and routine immunization. The CHWs are convened by the sub county assistant on a monthly basis to ensure they adhere to the household visits and note each action in the ttC household register. The visits are specified in Table 1.

### 2.7. Delivery of Services in the Control District

In the comparison area, the VHT provide care as usual, in accordance with the reporting framework and mandate [24] of the VHT in Uganda. After performing the routine household walks and identification of the household members in a given community, the VHT is supposed to map out the households with pregnant and lactating mothers and provide support, as these visits will contribute to the task accomplishment of the VHTs as required [25]. The details of the visits is detailed in Table 2 below: 

### 2.8. Sample Size

The sample size is calculated using the formula for comparing differences in rates and proportions between two groups and determining the number of subjects per group^n^, using an individual binary for a two-sided significant level α and power 1-β [27]. With an anticipated effect size of 10% [δBinary = (^μ^T − ^μ^C)], α = 0.05 (two-sided), β = 0.2,^ z^1^−α^/2 = desired significance level at 95% (0.05). ^Ζ^1 − β = desired power at 80% (0.842), type of test = two-sided, and absolute risk reduction = 10%.

Since the study focuses on uptake of pregnancy services and essential newborn care, the key participants are pregnant mothers. We, therefore, estimate the pregnancy rate from each area using the 2020 population estimates per district, then turning the pregnancy rate into a percentage proportion. To estimate pregnancy rate, the focus will be on the recommended women of reproductive age within the population. Using the health care planning estimation, it is estimated that 24% of the population are women of reproductive age [28]. An estimation of number of births, abortions and foetal losses was acquired from the actual total 2019 health management and information systems [29] reports for both districts. This provided a 1107-sample size in the two districts. This will be increased by 10% to 1218 participants to cater for a non-response. Therefore, the treatment and control groups will each have 609 mothers at the end of the study.

To determine number of clusters needed (n_cluster) [27,30]: n _cluster = total number of participants in the two groups (/fixed cluster size) which is (^n^Cluster_Binary 2)/m = 1218/60, giving us 20 clusters. In order to have the same number of clusters per arm, the number of clusters will be increased to the nearest upper even number, which is 20 in this study. This means that the sample size contains 1218 pregnant mothers in 20 clusters which is the sub-county by the administrative units of Uganda [31].

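### The 80% power for a 10-point difference is unsupported because no design effect is shown, and the cluster figures (20 or 22 clusters, 1200 or 1218 women) disagree

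*Protocol article*

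**What the plan says.** All references are to the protocol article.

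- **Section 2.8, formula.** The size per group is obtained "using an individual binary for a two-sided significant level α and power 1-β", with "α = 0.05 (two-sided), β = 0.2" and an absolute difference of 10%. The proportion put into the formula is described as a district pregnancy rate. Its value is not given, and no control-arm outcome rate is stated.
- **Section 2.8, total.** The result is 1107 women in the two districts. "This will be increased by 10% to 1218 participants to cater for a non-response", that is 609 per group.
- **Section 2.8, clusters.** The cluster step is "1218/60, giving us 20 clusters". It is followed by the statement that "the number of clusters will be increased to the nearest upper even number, which is 20 in this study".
- **Section 2.9.** 1218 women must complete, and drop-outs before six weeks after birth are replaced.
- **Section 2.10.** Sub-counties are the sampling units, 20 in all. "For each sub-county, six villages will be randomly selected, with each village providing 10 households".
- **Section 3.** The multivariate models will adjust for multi-level structure, described as clustering within villages.

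**The concern.** The power claim and the design do not match on the page. Women are sampled in blocks of about 60 per sub-county and the analysis will allow for correlation, but the only inflation described is the 10% for non-response. With 60 women per cluster, each 0.01 of ICC adds 0.59 to the design effect, so even a small ICC matters. If readers take the 80% at face value, a null result could be read as evidence against a 10-point benefit that the study had a much lower chance of detecting.

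Separately, the cluster count breaks the rounding rule stated beside it, and the sampling scheme does not produce the stated number of women. A reader cannot tell which figures the field team is to work to.

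**Working it through.** **1. The plan's own figures.** Section 2.8 gives z = 0.842 for 80% power; two-sided 5% gives z = 1.960. Individual-level size per arm:

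n = (1.960 + 0.842)² x [p1(1 − p1) + p2(1 − p2)] / 0.10²

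The outcome rates are assumptions. 45% v 55% gives the largest n for a 10-point difference. 60% (four antenatal visits) and 74% (skilled attendance) are national figures from the Background section.

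| Rates | Sum of variances | n per arm | Total | 1107 / total |
|---|---|---|---|---|
| 45% v 55% | 0.4950 | 389 | 778 | 1.42 |
| 60% v 70% | 0.4500 | 354 | 708 | 1.56 |
| 74% v 84% | 0.3268 | 257 | 514 | 2.15 |

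The 1107 is not reproduced. With a pooled variance the maximum is 784, and with a continuity correction 824. Raising power to 90% gives 1048 (1088 with continuity correction), still not 1107. The 1218 does reproduce: 1107 x 1.10 = 1217.7.

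**2. Cluster count and total.**
- 1218 / 60 = 20.3. The next even number up is 22, not 20.
- 20 sub-counties x 6 villages x 10 households = 1200, which is 18 fewer than 1218.

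**3. Power with 20 x 60 = 1200 women (600 per arm).** Design effect DE = 1 + (60 − 1) x ICC. Standard error = √{[p1(1 − p1) + p2(1 − p2)] x DE / 600}. Power is taken from the normal distribution and from a noncentral t on 20 − 2 = 18 df.

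Example, 60% v 70% at ICC 0.02: DE = 1 + 59 x 0.02 = 2.18; SE = √(0.45 x 2.18 / 600) = 0.0404; 0.10 / 0.0404 = 2.47; 2.47 − 1.96 = 0.51; power about 70%.

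Power in %, normal / t on 18 df:

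| ICC (assumed) | DE | 45% v 55% | 60% v 70% | 74% v 84% |
|---|---|---|---|---|
| 0.005 | 1.295 | 86 / 83 | 89 / 86 | 96 / 95 |
| 0.01 | 1.59 | 79 / 74 | 83 / 78 | 93 / 90 |
| 0.02 | 2.18 | 65 / 61 | 70 / 65 | 83 / 78 |
| 0.05 | 3.95 | 42 / 38 | 45 / 41 | 58 / 53 |

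Largest ICC at which power is still 80% (normal / t): 0.0092 / 0.0065 at 45% v 55%, 0.0118 / 0.0088 at 60% v 70%, and 0.0227 / 0.0185 at 74% v 84%.

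**4. Detectable difference from 60% with 80% power (normal / t):** 9.7 / 10.2 points at ICC 0.01, 11.3 / 11.9 at 0.02, and 14.9 / 15.7 at 0.05.

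**The case against.** **A design effect may already be inside 1107.** The total is 1.42 to 1.56 times the individual-level need at mid-range rates, and the DE at ICC 0.01 is 1.59. The numerator of the cluster formula carries a cluster label, and dividing an already inflated total by the cluster size is an ordinary last step. The article is also condensed. This stands in part: one cannot say that no ICC was ever used. But the text ties 1107 to the individual formula and a pregnancy rate, and names no inflation other than non-response.

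**Is the 80% simply not delivered?** A reader might infer so, but the documents do not support it. No ICC is given. With 1200 women, power is at or above 80% in all three scenarios at ICC 0.005, and at 74% v 84% it remains about 80% at ICC 0.02.

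**Section 3 speaks of villages, not sub-counties.** If all correlation lay within villages of 10, the tolerable ICC at 45% v 55% would be (1200/778 − 1) / 9 = 0.060. That would be reassuring, but sections 2.8 and 2.10 make the sub-county the cluster, so correlation between villages of one sub-county cannot be set aside.

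**Does 10% loss leave too few women?** One might compute 1218 x 0.9 = 1096, below 1107. That reading fails, because section 2.9 replaces drop-outs so that 1218 complete.

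**The count mismatch is trivial for power.** Agreed: 18 women in 1218 is 1.5%, and power at ICC 0.01 is about 83% (60% v 70%, normal) with either total. It is an inconsistency to reconcile, not a loss of power.

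**Conclusion.** The point holds in this form: the 80% power is unsupported as stated, not shown to be false. It depends on an ICC and an outcome rate that the article does not give. Under the assumed rates, 80% power is lost above an ICC of about 0.01 at 45-70% and about 0.02 at 74% v 84%. At ICC 0.05 it is about 38-58%, across the three rate scenarios and both reference distributions. The t on 18 df is itself a best case: treatment is assigned by district with one district per arm, so any difference between the two districts is inseparable from the treatment effect and is not counted in these figures.

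Two conflicts need no assumption. The rounding rule gives 22 clusters where the article states 20, and the sampling scheme gives 1200 women where sections 2.8 and 2.9 state 1218.

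**What to change.** 1. Keep 10 sub-counties per district. No extra women are needed.
2. In section 2.8, name the outcome and the control-arm rate behind the calculation, in place of the pregnancy rate. Show how 1107 arises, or withdraw it.
3. Restate power and detectable difference with design effect 1 + (m − 1) x ICC over a stated ICC range, for example 0.005 to 0.05. Label the reference distribution used (normal or t on 18 df) and say that one district per arm makes the figures a best case.
4. Delete or correct the sentence on rounding up to an even number.
5. Use one size in sections 2.8, 2.9 and 2.10: for example 20 x 60 = 1200, or 20 x 61 = 1220 with the village quota adapted to match.

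The cost is protocol wording and a stated power that will look less favourable. In return, a null result can be read against the difference that the study could actually detect.
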